# The Minnesota attributable risk of kidney donation (MARKD) study: a retrospective cohort study of long-term (> 50 year) outcomes after kidney donation compared to well-matched healthy controls

**DOI:** 10.1186/s12882-023-03149-7

**Published:** 2023-05-01

**Keywords:** Cohort studies, Follow-up studies, Kidney transplantation, Living donors, Nephrectomy

## Abstract

**Background:**

There is uncertainty about the long-term risks of living kidney donation. Well-designed studies with controls well-matched on risk factors for kidney disease are needed to understand the attributable risks of kidney donation.

**Methods:**

The goal of the Minnesota Attributable Risk of Kidney Donation (MARKD) study is to compare the long-term (> 50 years) outcomes of living donors (LDs) to contemporary and geographically similar controls that are well-matched on health status. University of Minnesota (n = 4022; 1st transplant: 1963) and Mayo Clinic LDs (n = 3035; 1st transplant: 1963) will be matched to Rochester Epidemiology Project (REP) controls (approximately 4 controls to 1 donor) on the basis of age, sex, and race/ethnicity. The REP controls are a well-defined population, with detailed medical record data linked between all providers in Olmsted and surrounding counties, that come from the same geographic region and era (early 1960s to present) as the donors. Controls will be carefully selected to have health status acceptable for donation on the index date (date their matched donor donated). Further refinement of the control group will include confirmed kidney health (e.g., normal serum creatinine and/or no proteinuria) and matching (on index date) of body mass index, smoking history, family history of chronic kidney disease, and blood pressure. Outcomes will be ascertained from national registries (National Death Index and United States Renal Data System) and a new survey administered to both donors and controls; the data will be supplemented by prior surveys and medical record review of donors and REP controls. The outcomes to be compared are all-cause mortality, end-stage kidney disease, cardiovascular disease and mortality, estimated glomerular filtration rate (eGFR) trajectory and chronic kidney disease, pregnancy risks, and development of diseases that frequently lead to chronic kidney disease (e.g. hypertension, diabetes, and obesity). We will additionally evaluate whether the risk of donation differs based on baseline characteristics.

**Discussion:**

Our study will provide a comprehensive assessment of long-term living donor risk to inform candidate living donors, and to inform the follow-up and care of current living donors.

**Supplementary Information:**

The online version contains supplementary material available at 10.1186/s12882-023-03149-7.

## Background

A living donor kidney transplant is the best treatment option for a patient with end-stage kidney disease (ESKD) as it provides better patient and graft survival and quality of life than either dialysis or a deceased donor transplant [1–13]. However, living donors (LDs) must undergo a major operative procedure associated with morbidity and mortality and the potential for adverse long-term consequences of living with a single kidney [14–58]. Practice guidelines, including those by the Kidney Disease: Improving Global Outcomes (KDIGO) consortium, allow a donor’s glomerular filtration rate (GFR) threshold to be as low as 60 ml/min/1.73m^2^ as an acceptance criterion for donation[59, 60]. The British Transplant Society 2018 guidelines and the European Renal Best Practice 2013 guidelines even allow GFR below 60 ml/min/1.73m^2^ in older donors[61, 62]. Since postdonation GFR is about 65% of the predonation value due to hypertrophy of the retained kidney, many LDs will have a GFR less than 60 ml/min/1.73m^2^ early after nephrectomy. For others, a decrease of GFR with aging or new onset disease will subsequently result in GFR less than 60 ml/min/1.73m^2^. Numerous studies in the general population have shown that individuals with GFR of less than 60 ml/min/1.73m^2^ have increased long-term risks including continuing loss of kidney function and higher rates of cardiovascular disease (CVD) and mortality [63–87]. Those observations may not be relevant to LDs who have an abrupt, isolated reduction in GFR in the absence of any underlying disease process or comorbid illness [88–93].

### Existing studies of attributable long-term risk of kidney donation

Several studies have sought to estimate the attributable risk of donor nephrectomy on mortality, ESKD, CVD, and other outcomes. Single-center and registry studies comparing LDs to the general population have not shown increased long-term CVD, ESKD, or mortality risk [14, 44–54]. Indeed, studies of longitudinal renal function in LDs have shown a small annual increase in GFR or estimated GFR (eGFR) for more than 15 years after donation [94–98]. A number of studies with average follow-up of less than 10 years compared LDs to matched healthy controls and found no difference in CVD and mortality [52–54, 58]. However, a 2014 Norwegian study with a median follow-up of 18 years found increased CVD and mortality in LDs compared to healthy controls; the authors attributed the difference in their findings compared to prior ones to longer follow-up [55]. A subsequent study based on the same population reported an increased risk of ischemic heart disease in LDs [99]. Two studies – the 2014 study from the Norwegian group, the other from the United States (US) - reported an increased risk of ESKD among LDs [55, 56]. Studies of postdonation pregnancies, compared to the general population, have generally not identified an increased risk of adverse fetal or neonatal outcomes. However, two studies comparing postdonation to predonation pregnancies reported an increased risk of hypertensive complications in the postdonation pregnancies, and one study reported an increased risk of hypertensive complications compared to healthy selected non-donors [100–102].

### Limitations of prior work

In a review of studies reporting increased long-term risk for LDs, Janki et al. identified that both the Norwegian study reporting an increased risk of CVD, mortality, and ESKD, and the US study reporting increased risk of ESKD, selected non-donor control populations that were healthier than the donors, resulting in an over estimation of risk [103]. In addition, the definition of ESKD differed between donors and non-donors in the US study, potentially biasing the results. A meta-analysis of the cardiac studies concluded that there was no increase in CVD disease or mortality in LDs [104]. For the two studies identifying an increased risk of ESKD among LDs, the number of events was small, and there have been additional concerns about methodology, including: controls were non-contemporaneous and from a different geographic location; lack of renal function assessment for controls at the date corresponding to the date of donation; and concerns about the choice of statistical methods [105–115].

A key limitation in existing studies is that there was no determination of family history of chronic kidney disease (CKD) or ESKD for controls. In the Norwegian study, all 9 donors who developed ESKD were first-degree relatives of the recipient; in the US study, 83 of the 99 who developed ESKD were related to the recipient. Numerous studies in the general population have shown that individuals related to a person with ESKD have an increased risk of ESKD [116–122]. Wainright et al., using the Organ Procurement and Transplantation Network (OPTN) database, reported that LDs who were first-degree relatives of the recipient had significantly increased risk of ESKD (highest in identical twins) compared to LDs who were distant relatives or were unrelated to the recipient [123].

There have only been a few studies of pregnancy risk postdonation [100–102, 124, 125]. Studies have been limited by low numbers of events, and the design has generally been restricted to a before-and-after study design which may result in an over estimation of risk.

Finally, to date, most studies of LDs matched to healthy controls had limited follow-up. In the US study by Muzaale et al.,[56] the mean follow-up was 7.2 years, and in the Norwegian study, the median follow-up was 15.1 years. Steiner has emphasized that long-term follow-up is necessary to determine if kidney donation is associated with ESKD risk, since most LDs are relatively young at donation and most ESKD develops later in life [126–128]. In addition, the majority of kidney diseases progress slowly, so that short-term LD follow-up will only identify LDs developing rapidly progressive disease (e.g., immunologic). Long-term follow-up is required to determine the impact of diseases associated with aging, specifically hypertension and diabetes mellitus (DM), the two most common causes of ESKD in the US general population and the US LD population [129]. Analyses of US national LD data (20-year follow-up) and University of Minnesota (UMN) LDs have shown that the rate of ESKD increases postdonation; and, specifically, the cumulative incidence of ESKD due to DM or hypertension increases many years after donation [130, 131]. Thus, short-term studies will miss most postdonation ESKD.

The recognition of significant gaps in our understanding of long-term LD outcomes has resulted in calls for more complete long-term LD follow-up studies [132]. In the US, this is reflected in statements from the Advisory Committee on Organ Transplantation[132], The Organ Donation and Recovery Improvement Act (ODRIA (P.L. 108–216) (Sect. 7) and (Sec 371 A)[133], and by the Health Resources and Services Administration in testimony to Congress[134] and on its website [135]. Consensus conferences have argued for continued, systematic collection and reporting of long-term LD outcomes [136, 137]; reasons included: (a) LDs and their potential recipients need accurate outcome information for informed consent, and (b) donation is a public trust, and the community has an obligation to continue to collect detailed information on outcomes. And, importantly, LDs themselves are asking for this information [138–141]. Of concern, between 2004 and 2019 (because of the pandemic the number of LDs decreased in 2020 and 2021) the number of LDs has only increased 3%[129]; it has been suggested that the uncertainty regarding LD risk may be partly responsible.

To address these calls to action and limitations of existing studies, the Minnesota Attributable Risk of Kidney Donation (MARKD) study will compare the long-term risks for LDs from UMN and Mayo Clinic (first donation in 1963 and up to 60 years of follow-up) to the long-term risks for contemporaneous, geographically similar, healthy matched controls from the Rochester Epidemiology Project (REP). By reviewing medical records, we additionally plan to identify a subset of controls from the REP with known normal kidney function at a date corresponding to the date of donation and known family history of CKD and be able to match controls to LDs on these important risk factors. Consequently, we will provide the best data to date to inform prospective candidates of the long-term risks of kidney donation.

## Methods

### Overview of study design

This is a matched cohort study of LDs from UMN and Mayo Clinic with contemporaneous, chart-validated, healthy matched REP controls with an index date (date of donation for LD) between 1963 and 2012. This time frame was chosen since the focus of the study is on long-term (> 10-year postdonation) outcomes (see Fig. 1). New outcome data will be ascertained from national registries, including the National Death Index (NDI, mortality), United States Renal Data System (USRDS, ESKD), and a new survey of health outcomes. The new data will be augmented with information collected from prior surveys (UMN LDs) and medical record review (UMN LDs and REP controls). Study criteria for donors includes: 1) provided research authorization and 2), US residency. Known non-US residents will be excluded from donor and control cohorts since national database information is unavailable for these individuals.

**Fig. 1 Fig1:**
[figure not shown]
Matched Cohort Study Design

### Aims and hypotheses

The MARKD study aims to determine long-term attributable LD risk by comparing well-matched controls with LDs. LDs will be compared with matched controls to determine: (a) whether LDs are at greater risk for the rare outcomes of mortality and ESKD; (b) whether LDs are at increased risk for CVD, cardiovascular mortality, and/or increased risk of intermediate measures of kidney disease (proteinuria, CKD [eGFR < 45 and eGFR < 30 ml/min/1.73m^2^ ]); (c) whether the trajectory of eGFR differs between LDs and controls; d) whether there are differences in the above outcomes for those developing de novo kidney disease and/or disease that might affect the kidneys (e.g., hypertension, DM, proteinuria); and e) whether there are differences in pregnancy outcomes (e.g., preeclampsia) between LDs and controls. The overall hypothesis is that LDs will have relatively small, slightly increased, but clinically insignificant, differences in the incidence of ESKD, mortality, intermediate endpoints, and pregnancy complications compared to well-matched control groups.

### Study cohorts

#### UMN LD cohort

From January 1, 1963 through December 31, 2012, there were 4022 LDs at UMN who met the study criteria. Most LDs were from the upper Midwest region of the US, and detailed descriptions of the UMN LD cohort have been published [45, 50]. At donation, laboratory and demographic variables, surgical information, and peri-operative course information is collected. Prior to 2003, LDs were surveyed intermittently. In 2003, all donors were contacted to be surveyed and asked to consent to be surveyed every three years. Since 2003, consenting LDs are surveyed postdonation at regular intervals (6, 12, and 24 months, and then every 3 years). Those not returning to the clinic are sent a survey (by mail; or, if preferred, by email) to determine health status. If the survey is not returned, the LD is contacted by phone monthly, for 3 months. At least one phone call is made in the evening and one on weekends to increase response rates. LDs are also asked to provide alternate contacts. For LDs who become lost to follow-up UMN uses these contacts to ask for a current phone number and address. Available internet search engines and other databases (e.g., Accurint.com, Peoplefinder.com) are also used to identify LDs lost to follow-up.

At each contact, LDs are asked about hypertension, DM, and other diagnoses requiring treatment. Female donors are asked about pregnancy history. LDs are also asked to provide recent lab test results and copies of medical records; alternatively, with LDs’ permission, UMN investigators contact local clinics for recent medical records that include clinical notes and laboratory test results, including serum creatinine, glucose, urinalysis, and urinary protein measurements. Those without recent information are asked to get a history, physical, and labs at their local physician’s office and have the results sent to UMN. For LDs willing to do the tests but without insurance coverage, UMN pays for them. A summary of the clinical and demographic characteristics of the UMN LD cohort is given in Table 1.

**Table 1 Tab1:** Characteristics of the University of Minnesota (UMN) and Mayo Clinic donors

	UMN donors (N = 4022)	Mayo donors (N = 3035)
Years from donation to last survey or History & Physical (mean ± SD)	22.04 ± 11.93	
No returned surveys	9.5%	
Sex (%)		
Female	2294 (57.0%)	1668 (55.0%)
Male	1728 (43.0%)	1354 (44.6%)
Unknown	0 (0%)	13 (0.4%)
Age at donation (mean ± SD)	39.02 ± 11.64	42.52 ± 11.98
Unknown	0 (0%)	13 (0.4%)
Race (%)		
Asian	40 ( 1.0%)	31 (1.0%)
Black or African American	95 ( 2.4%)	50 (1.6%)
Caucasian / White	3796 (94.4%)	2840 (93.6%)
Hawaiian Or Other Pacific Islander	1 ( 0.0%)	4 (0.1%)
Multi-racial	90 ( 2.2%)	26 (0.9%)
Unknown	0 (0%)	84 (2.8%)
Ethnicity (%)		
Hispanic/Latino	99 ( 2.5%)	66 (2.2%)
Non-Hispanic/Non-Latino	3428 (85.2%)	2600 (85.7%)
Unknown	495 (12.3%)	369 (12.2%)
Index decade (%)		
1960s	99 ( 2.5%)	45 (1.5%)
1970s	658 (16.4%)	271 (8.9%)
1980s	796 (19.8%)	218 (7.2%)
1990s	1040 (25.9%)	454 (15.0%)
2000s	1200 (29.8%)	1647 (54.3%)
2010–2012	229 ( 5.7%)	400 (13.2%)
Donor relationship (%)		
Child	474 (11.8%)	493 (16.2%)
Parent	932 (23.2)	422 (13.9%)
Full Sibling	1579 (39.3%)	934 (30.8%)
Half Sibling	21 ( 0.5%)	25 (0.8%)
Identical Twin	15 ( 0.4%)	5 (0.2%)
Not Related	562 (14.0%)	662 (21.8%)
Other Relative	241 ( 6.0%)	156 (5.1%)
Spouse	198 ( 4.9%)	327 (10.8%)
Unknown	0 (0%)	11 (0.4%)
Creatinine at donation (mean ± SD)	0.91 ± 0.16	0.90 ± 0.19
Unknown	0.7%	1.1%
BMI at donation (mean ± SD)	25.88 ± 4.36	27.38 ± 5.11
Unknown	1.5%	0.5%
Glucose at donation (mean ± SD)	93.46 ± 14.77	96.00 ± 14.12
Unknown	4.9%	1.0%
DBP at donation (mean ± SD)	73.26 ± 9.92	73.16 ± 12.22
Unknown	1.9%	4.8%
SBP at donation (mean ± SD)	119.85 ± 13.11	120.62 ± 15.22
Unknown	1.9%	4.8%

#### Mayo clinic LD cohort

Between 1963 and December 31, 2012, 3035 LD transplants were performed who met the study criteria, with most LDs from the upper Midwest region of the US. The acquisition and storage of all relevant clinical data for all LDs are currently available via the Transplant Center clinical databases, which interfaces with the institution’s electronic medical record to access laboratory and demographic variables, surgical information, and peri-operative course. The Mayo Clinic LD program provides an additional source of long-term LD follow-up that will: (a) increase the sample size to increase the statistical power for analyses of certain outcomes (ESKD and mortality) and (b) add a second site to assess the generalizability of findings. A summary of the clinical and demographic characteristics of the Mayo LD cohort is given in Table 1.

#### Rochester epidemiology project

The development and use of the REP have been described in detail [142–145]. In brief, the REP is a medical records linkage system that allows detailed collection of data on a well-defined population (Olmsted and surrounding Counties, Minnesota, US) starting in the early 1960s. The REP was developed with the recognition that nearly all residents of Olmsted County received their medical care at one of two hospitals and/or at affiliated institutions because of the central location of the hospitals in an area in which there are no other competing medical centers. In addition, other small private practices have partnered with the major medical centers in the area to contribute to the REP. As such, population estimates for the Olmsted County by REP are slightly higher and more comprehensive than those reported in the US Census (1970, 104.1%; 1980, 103.5%; 1990, 102.4%; and 2000, 102.7% of the US Census counts) [144]. The characteristics of the population are similar to those of residents from the Upper Midwest of the US [145, 146]. The records contain details of every inpatient hospitalization at the affiliated hospitals, every outpatient visit to the office, clinic, or emergency department, as well as every laboratory result and correspondence concerning each patient. The medical records are easily retrievable because the REP has maintained extensive indices based on clinical and histologic diagnoses (i.e., diagnosis codes) and surgical procedures. The result is the linkage of medical records from nearly all sources of medical care utilized by the Olmsted County population. Each year, more than half of the population is examined at one of the REP facilities, and about 85–100%, depending on the age group, have at least one REP contact over a 3-year period [142].

The REP represents the same geographical region as both the UMN and Mayo LDs with the same time frame starting in the 1960s, making it an ideal control group (reference cohort) for long-term follow-up.

### Control matching algorithm, validation, and abstraction

Our goal is to identify, for each LD, individuals in the REP database who would have been eligible for kidney donation on the same date as the LD based on the information in the medical record.

*Pilot studies*:

As we were unsure of the most efficient way to use diagnostic codes and chart abstraction for excluding controls that would not qualify as donors, we performed two pilot studies to optimize our selection of exclusionary codes and exclusionary criteria on chart abstraction.

First, we identified all approximately 180,000 individuals who have not opted out of the use of their medical records for research (per Minnesota statute) in the REP Olmsted County cohort with a potential index date within the age and time period window of the donors. Within the REP, code sets have been developed for 355 different specific diseases using International Classification of Disease 9th and 10th revisions (ICD-9, ICD-10), Hospital Adaptation of the International Classification of Diseases (HICDA), and Berkson codes (a local coding system that predates ICD-9 codes). On review of these code sets, we determined that 173 of these were conditions/diseases that if truly present, would always lead to exclusion as a donor. Of these exclusionary diseases, 26 were prevalent on or prior to the index date of at least 1,000 individuals within the REP. However, we did not want to exclude too many of our potential controls that were false positives for these exclusionary diseases. Thus, we (Drs. [name] and [name]) performed a manual chart review on 10 random individuals for each of these disease code sets. We found that some codes within these code sets corresponded to conditions that were true contraindications for donation (e.g., kidney disease), but some were for mild disease or other conditions which were not absolute contraindications (e.g., urinary incontinence that was mild, depression that was mild and transient, arrhythmias – palpitation with negative cardiac workups). The individual codes for these 26 code sets were refined to better correspond to conditions that would be absolute contraindications for donation. Subsequently, all 173 exclusionary diseases (including the 26 that were adjusted to be made more specific for exclusion and less sensitive) were used to exclude individuals from being matched as controls. See **Supplemental Materials** for a full list of exclusionary conditions.

Second, after excluding individuals with these 173 diseases, we performed a pilot study of 117 randomly sampled individuals to abstract in detail their medical status, available data at or prior to the potential index date and during follow-up, and any potential concerns with their candidacy as a kidney donor on the index date. From this pilot study, we identified 5 exclusionary conditions (psychiatric conditions, substance abuse, hypertension, abnormal serum creatinine or urine protein, and obesity) that were relatively common and missed by the exclusionary code set. Psychiatric conditions, substance abuse, and hypertension are common and require medical record review as many are mild and do not warrant exclusion. Abnormal serum creatinine, urine protein, or body mass index (BMI) are simply underdiagnosed and, thus, require medical record review to be detected for exclusion.

#### Initial matching algorithm

After finalizing the list of exclusionary codes, up to 4 potential controls were identified for every donor. All controls were residents of Olmsted County (or surrounding counties) at some point and lacked any exclusionary diagnoses before the index date (date of donation for the matched LD) or up to 1 year after the index date. The 1-year window after the index date was used because some diseases may be present on the index date but not diagnosed due to the intermittent nature of clinic visits in the medical record. This matching was accomplished first for the UMN donors and then for the Mayo Clinic donors. These potential REP controls were initially identified based on the following requirements: (1) Olmsted County or surrounding county resident at index date, (2) at least one REP encounter prior to index and at least one REP encounter one year or more after index, (3) age difference between LD and potential REP control at index less than 5 years, and (4) exact match on broad racial categories (Black vs. non-Black). If more than four controls meet these criteria, the four best controls based on (1) exact match on more granular racial categories (White or unknown, Black, Asian, Hawaiian/Pacific Islander, Other), (2) exact match on ethnicity (Hispanic, non-Hispanic), and (3) minimum difference in age at index was selected. If fewer than four controls were identified, the matching criteria were broadened to allow for unknown county of residence at the index date and subsequently known non-resident of Olmsted or surrounding counties at the index date. The full algorithm is provided in Fig. 2. From this initial algorithmic matching over 16,000 and 14,000 potential controls were identified for the UMN and Mayo Clinic donors, respectively.

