#### Statistical analyses details

Log-rank tests and Kaplan Meier curves will be used as preliminary assessments to compare the risk of all-cause mortality and cardiovascular mortality, CVD, ESKD, CKD (eGFR < 45; eGFR < 30 ml/min/1.73m^2^), proteinuria, DM, and hypertension after index date between LDs and healthy controls. Our study is powered based on these analyses. Cox proportional hazards models will also be used to test for an increased risk of adverse outcomes in living LDs versus controls while directly accounting for the variables used for matching (to account for any possible residual imbalance between the cohorts similar to how one may adjust for characteristics in a randomized controlled trial to account for residual imbalance and to improve efficiency). In analyses involving Mayo LDs and their associated controls we will account for donation center (Mayo vs. UMN) as a covariate in the model. If the proportional hazards assumption fails, an alternative method such as an accelerated failure time model will be considered. Indeed, the risk of mortality and ESKD may disproportionately increase with long-term follow-up on the 60-year scale of this study [123, 130, 131]. A similar approach will be used to test for increased risk of outcomes for LDs versus controls after development of DM, hypertension, proteinuria, de novo kidney disease, or pregnancies with gestational hypertension or preeclampsia, but additional measures (e.g. matching, adjustment) will be used to account for the time of disease onset.

In order to evaluate biases in the selection of controls and ascertain outcomes, we will compare the risk of non-kidney-related cancer between donors and controls using the previously described methods. As cancer risk is lower in donors than the general population, we expect a similar lower risk in controls [150]. If controls are well matched, we do not expect the risk of non-kidney related cancer to differ between donors and controls. If a difference in cancer risk is identified, it may indicate imbalance in our matching and it will be further investigated using methods described in Shi et al. [151].

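### Controls, but not donors, must survive at least one year past the index date, yet mortality is compared from that date: a modest, avoidable bias against donation

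*Protocol article*

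**What the plan says.** Under Initial matching algorithm, a potential control needs "at least one REP encounter prior to index and at least one REP encounter one year or more after index". The same section says that the controls "lacked any exclusionary diagnoses before the index date (date of donation for the matched LD) or up to 1 year after the index date". The reason given for the one-year diagnosis window is that "some diseases may be present on the index date but not diagnosed due to the intermittent nature of clinic visits". No reason is given for the later-encounter rule. When fewer than four controls are found, only residence is relaxed: "the matching criteria were broadened to allow for unknown county of residence at the index date".

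For donors, Overview of study design sets out: "Study criteria for donors includes: 1) provided research authorization and 2), US residency". It adds nothing about survival, contact or diagnoses after donation.

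Under Statistical analyses details, the log-rank and Kaplan-Meier comparisons of mortality, ESKD, CVD and the other event outcomes are made "after index date between LDs and healthy controls", and Cox models follow. No landmark, delayed entry or shifted time origin is described. For the negative control, the same section states that "we will compare the risk of non-kidney-related cancer between donors and controls" with the same methods.

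**The concern.** Eligibility of controls depends on what happens after their time zero. A person who died in the first year, or died later without another visit, could never have become a control. A donor who died in the first year stays in and counts as an event. This is immortal time in one arm only, and for death it can only push the estimate towards harm from donation.

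The size matters because the study looks for small effects. Its hypothesis is a slight increase in risk, it is powered for a mortality hazard ratio of 1.13 to 1.16, and the Dissemination section plans a risk calculator for candidate donors. Limitations of prior work faults earlier studies for choosing controls healthier than the donors and so overestimating risk; this rule pushes the same way. The control groups for sensitivity analysis, and the analysis requiring five years of prior history, are not said to lift either condition, so they would not clearly expose the problem.

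**Working it through.** **Inputs.** Donors: 4022 + 3035 = 7057, of whom 98% are matched, about 6916 (Power). Deaths: 11% (Power). Mean follow-up: 22 years, from the UMN figure of 22.04 in Table 1. Using it for the whole cohort is an assumption. The rate at which the hazard grows is not in the article, so it is varied: 0, 5% and 9% per year.

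**The plan's own figure.** Schoenfeld, two-sided 5%, 80% power: HR = exp[(1.960 + 0.842)/√(D·p·(1−p))], where D is deaths and p the donor share.
- 3:1: D = 4 × 6916 × 0.11 = 3043, D·p·(1−p) = 3043 × 0.1875 = 570.6, HR = 1.124 (stated 1.13).
- 1:1: D = 1522, D·p·(1−p) = 1522 × 0.25 = 380.4, HR = 1.154 (stated 1.16).

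Power at the stated ratios is 83.1% and 82.5%, so they are slightly conservative. At 10.5% deaths the formula gives 1.128 and 1.158, which round to the stated pair. The yardstick is sound.

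**Share of expected deaths in the guaranteed year.** With the hazard proportional to exp(g·t), the share of the cumulative hazard to year T that falls in year 1 is f = (e^g − 1)/(e^(gT) − 1), or 1/T when g = 0. The level of the hazard cancels. For g = 0.09 and T = 22: f = 0.0942/6.243 = 1.51%.

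**Null hazard ratio.** Controls lose a share f of their expected deaths but keep the time at risk, so with no true effect HR ≈ 1/(1 − f). The log-rank statistic shifts by ln(HR)·√(D·p·(1−p)), which gives the two-sided type I error.

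| Hazard growth per year | f | Null HR | ln HR ÷ ln 1.13 | Type I error, 3:1 | Type I error, 1:1 |
|---|---|---|---|---|---|
| 0 | 4.55% | 1.048 | 38% | 19.9% | 14.8% |
| 5% | 2.56% | 1.026 | 21% | 9.5% | 8.0% |
| 9% | 1.51% | 1.015 | 12% | 6.5% | 6.0% |

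**Simulation check.** 6916 donors, 3:1, 11% deaths, follow-up averaging 22 years, no true effect, 400 replicates. With the clock at index, the hazard ratios were 1.047, 1.027 and 1.016 (growth 0, 5%, 9%), with type I error 21%, 8.5% and 5.5%. With both groups restricted to those still under observation and event-free at one year, the hazard ratios were 1.002, 0.999 and 1.001, with type I error about 5% in each case. Delayed entry beyond one year was not simulated.

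**Sensitivity.** Over 10 to 30 years of follow-up and growth of 0 to 9%, the analytic null HR runs from 1.007 to 1.11. If the qualifying encounter came at two or three years for everyone, f at 9% growth would be 3.2% or 5.0%, giving a null HR of 1/(1 − 0.032) = 1.03 or 1/(1 − 0.050) = 1.05.

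**The case against.** **The diagnosis window has a purpose.** Donors were extensively evaluated and controls were not, so removing disease that was present but unrecognised at index makes the groups more alike. This stands: for diagnosed outcomes, part of what the window removes ought to be removed, and the net bias there is not established. It does not excuse the later-encounter rule, which alone guarantees survival.

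**The size is small.** Mean age at donation is about 40 and mortality rises with age, so the lower end of the range is the more plausible for death, with type I error only a little above 5%. For ESKD, the Background says that the rate rises after donation, so a constant hazard would overstate the first-year share. Both points stand and are why the bias is called modest.

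**The focus is long-term.** The article explains its range of index dates by an interest in outcomes beyond ten years. That is not a landmark; the comparison is still stated from the index date.

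Two stronger readings are tempting. A reader might infer that every hazard ratio and incidence rate is biased. The documents do not support that: the pilot work found that hypertension, abnormal creatinine or urine protein, and obesity were commonly missed by the code sets, and chart validation looks only at records before index. First-year events of those kinds are not clearly excluded in controls, and the eGFR and pregnancy models are not shown to be affected. A reader might also infer that first-year cancers certainly disqualify controls. Recent cancer is named only under chart validation, and the list of 173 conditions is in supplementary material not shown, so that point stays conditional.

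**Conclusion.** The defect holds for all-cause and cardiovascular mortality, and in year 1 for any outcome whose codes are among the 173 exclusions (kidney disease is named as a true contraindication). For mortality the direction is towards excess risk in donors. With one guaranteed year and 22 years' mean follow-up, the null mortality hazard ratio is about 1.015 to 1.05, or 12% to 38% of the log of the detectable ratio of 1.13. This rests on the assumed hazard growth and on applying the UMN follow-up to the whole cohort; shorter follow-up or later qualifying encounters make it larger. If cancer codes are among the exclusions, the negative control can show a difference that the selection rule itself created. The bias is not large enough to overturn a strong result, but it is one-sided for mortality and falls on the small effects that the study expects.

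**What to change.** Keep the selection rule and change the time origin. For mortality, and for outcomes whose codes are among the exclusions:
- start the clock at index plus one year in both groups;
- include donors who are alive, and free of the outcome being analysed, at that point;
- let each control enter the risk set at its first encounter at or after one year (delayed entry), and state how an outcome first recorded at that encounter is handled;
- apply the same landmark to the cancer negative control;
- report donors' first-year events separately and descriptively, so that perioperative harm stays visible.

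Do not remove donors for first-year exclusionary diagnoses in general. Some, notably renal ones, may result from donation: the Background notes that many donors have a GFR below 60 early after nephrectomy. Removing them would bias towards no effect. The article also shows no comparable diagnosis source for the Mayo donors, who were not routinely contacted about health outcomes and will not be surveyed.

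The cost is a change to the analysis text and code, with no rematching, plus the dates of controls' qualifying encounters. The downside is that donors' first-year events leave the comparative estimate, which then describes risk from one year onward.
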